## Abstract

**Background:**

Radical surgery is the mainstream treatment for patients presenting with advanced primary or recurrent gastrointestinal cancers; however, the rate of postoperative complications is exceptionally high. The current evidence suggests that improving patients’ fitness during the preoperative period may enhance postoperative recovery. Thus, the primary aim of this study is to establish the effectiveness of prehabilitation with a progressive, individualised, preoperative exercise and education program compared to usual care alone in reducing the proportion of patients with postoperative in-hospital complications. The secondary aims are to investigate the effectiveness of the preoperative intervention on reducing the length of intensive care unit and hospital stay, improving quality of life and morbidity, and reducing costs.

**Methods:**

This is a multi-centre, assessor-blinded, pragmatic, comparative, randomised controlled trial. A total of 172 patients undergoing pelvic exenteration, cytoreductive surgery, oesophagectomy, hepatectomy, gastrectomy or pancreatectomy will be recruited. Participants will be randomly allocated to prehabilitation with a preoperative exercise and education program (intervention group), delivered over 4 to 8 weeks before surgery by community physiotherapists/exercise physiologists, or usual care alone (control group). The intervention will comprise 12 to 24 individualised, progressive exercise sessions (including aerobic/anaerobic, resistance, and respiratory exercises), recommendations of home exercises (16 to 32 sessions), and daily incidental physical activity advice. Outcome measures will be collected at baseline, the week prior to surgery, during the hospital stay, and on the day of discharge from hospital, and 1 month and 1 months postoperatively. The primary outcome will be the development of in-hospital complications. Secondary outcomes include the length of intensive care unit and hospital stay, quality of life, postoperative morbidity and costs.

**Discussion:**

The successful completion of this trial will provide robust and high-quality evidence on the efficacy of a preoperative community- and home-based exercise and education intervention on important postoperative outcomes of patients undergoing major gastrointestinal cancer surgery.

**Trial registration:**

This trial was registered prospectively with the Australian New Zealand Clinical Trials Registry (ACTRN12621000617864) on 24th May 2021.

## Background

For a selected group of patients presenting with advanced primary or recurrent cancers within the pelvis or abdomen, complex and extensive surgery may offer the only chance of long-term survival [1, 2]. Despite the survival benefit, the development of in-hospital postoperative complications after radical surgical resection with the intent of clear surgical margin remains very high [3]. For patients undergoing pelvic exenteration, cytoreductive and advanced upper gastrointestinal cancer surgeries, postoperative complication rates can range from 40 to 70% [4, 5] and comprise debilitating complications, including anastomotic leak, ileus, wound infection, sepsis, severe bleeding and pneumonia [6, 7]. These are major complications which require intensive treatment, prolonging hospital stay, reducing patient’s quality of life [1, 8, 9] and increasing the cost of care [10, 11].

Recent evidence suggests that the patient’s preoperative status largely determines the risk of developing postoperative complications following cancer surgery [12]. Patients presenting a low level of physical fitness during the preoperative period were more likely to develop postoperative complications [13, 14] while higher levels of self-reported physical activity were associated with improved postoperative outcomes [15]. Over the past decade, preoperative exercise has gained popularity, with the intent of strengthening functional capacity before surgery, accelerating the return to the preoperative conditions. To date, several randomised controlled trials (RCTs) have been conducted to investigate the effectiveness of a wide range of preoperative exercise programs in reducing postoperative complications and length of hospital stay in patients undergoing cancer surgery [16].

A recent systematic review and meta-analysis identified 13 unique clinical trials (including 806 patients) investigating the effectiveness of prehabilitation with preoperative exercise in patients that underwent surgical resection for colorectal, liver, oesophageal, lung, oral, and prostate cancer [17]. Most of the patient cohorts, comprised of single, small and underpowered trials. In patients undergoing lung cancer surgery, preoperative exercise effectively reduced postoperative complications by approximately 50% and hospital length of stay by almost 3 days compared to no treatment control. Other more recent trials reported similar results and strengthened this body of knowledge. For example, an RCT investigating the efficacy of prehabilitation, including endurance exercise and promotion of physical activity in a mixed group of 125 patients (including non-cancer patients) undergoing abdominal surgery, reported a significant increase in aerobic capacity and subsequent reduction in postoperative complications by over 50%, when compared to standard care [18]. Similarly, a multicentre, RCT involving 441 patients undergoing upper abdominal surgery investigated the effectiveness of preoperative breathing exercises [19]. This trial demonstrated a reduction of 52% in postoperative pulmonary complications in the preoperative intervention group compared to the control group.

Despite these previous studies providing evidence in support of preoperative exercise to improve postoperative outcomes, this evidence-base is limited by small sample sizes [20–24], the inclusion of mixed populations and heterogeneous surgical types (cancer/non-cancer) [18], comprehensive to state hospital-based intervention and exclusion of regional-rural patients who cannot travel [18] and other methodological flaws such as failure to conceal allocation and lack of intention-to-treat analyses. Therefore, the role of preoperative exercise for patients undergoing major advanced or recurrent gastrointestinal surgery is still unclear [25].

To overcome this paucity of robust evidence, our team conducted a pilot RCT, which demonstrated the feasibility and acceptability of a preoperative exercise program in patients undergoing major gastrointestinal cancer surgery to inform this large RCT: The Priority Trial [26].

The primary aim of this full-scale RCT is to establish the effectiveness of prehabilitation with a progressive, individualised, preoperative exercise and education program (compared to a usual care study arm) in reducing the proportion of patients with postoperative in-hospital complications within the primary admission of the index surgery. Our primary hypothesis is that the preoperative intervention with exercise and education will reduce the proportion of patients with postoperative in-hospital complications compared to usual care. The secondary aims are to investigate whether a preoperative exercise and education program, compared to usual care, reduces the length of intensive care and hospital length of stay, improves postoperative patient quality of life, and reduces postoperative morbidity. Furthermore, this trial seeks to determine the cost-effectiveness of the preoperative exercise and education program.

## Methods/design

This protocol was written in accordance with the Consolidated Standard of Reporting Trials (CONSORT) [27, 28], followed recommendations from the Standard Protocol Items: Recommendations for Interventional Trials (SPIRIT) Checklist [29, 30] and has been prospectively registered with the Australian New Zealand Clinical Trials Registry (ACTRN12621000617864). Ethics approval has been obtained from the Sydney Local Health District Human Research Ethics Committee – Concord Hospital (2019/ETH13718).

### Trial design

The proposed study is a multi-centre, assessor-blinded, pragmatic, comparative, RCT, with two parallel groups randomised in a 1:1 allocation. Participants will be randomised to (i) a progressive, preoperative exercise and education program delivered over 4 to 8 weeks prior to surgery or (ii) usual perioperative care alone (Fig. 1).

**Fig. 1 Fig1:**
[figure not shown]
PRIORITY TRIAL flow chart

### Study sites

This multicentre trial will be performed in three centres in Australia: Royal Prince Alfred Hospital (leading trial site) and the Chris O’Brien Lifehouse (satellite site) in Sydney, and the Peter MacCallum Cancer Centre in Melbourne. These sites are nationally recognised as leading centres for managing patients undergoing major advanced primary or recurrent gastrointestinal cancer surgery in Australia.

### Participants

A total of 172 consecutive participants undergoing major advanced primary or recurrent gastrointestinal cancer surgery will be included. To be eligible to enter this trial, all participants must satisfy the following inclusion and exclusion criteria:

Inclusion criteria:

(i)Adult patients (18-80 years) undergoing elective major surgery for advanced or recurrent gastrointestinal cancer, including pelvic exenteration (advanced primary or recurrent pelvic cancers), cytoreductive surgery, oesophagectomy, hepatectomy, gastrectomy or pancreatectomy;(ii)Consult a gastrointestinal surgeon at least 4 weeks before planned surgery.

Exclusion criteria:(i)Cognitive impairment such that they are unable to provide informed consent;(ii)Co-morbidity preventing participation in exercise and physical assessments (i.e., cardiorespiratory, musculoskeletal, neurological);(iii)Presenting with very poor functional capacity. Defined as a score of ‘zero’ (i.e., No) to all the following Duke Activity Status Index (DASI)(31) questions:Can you climb a flight of stairs or walk up a hill?;Can you do heavy work around the house?;Can you do yard work?;Can you participate in strenuous sports?(iv)Inadequate English language to complete outcome measures;(v)Currently participating in an exercise program.

### Participant recruitment and mode of contact

Surgeons, Anaesthetists, Allied Health practitioners, Clinical Research Managers, and Research Officers from the participating institutions will be involved in patient identification and screening. All patients will be screened for inclusion and exclusion criteria. Eligible patients will be provided with a patient information sheet. If they are interested in participating, they will provide consent for a researcher from the trial to contact them and discuss the trial further. An adequate time (24 h from initial contact) will be provided for all patients to understand and consider what the trial is proposing and for their questions and concerns to be addressed. After this period, the trial’s research officer will seek consent from patients. Clinical assessment and decision-making will proceed according to usual clinical protocols. The number of patients screened and reasons for ineligibility in the study will be documented. After signed consent is obtained, participants will be contacted by an authorised member of the study team at baseline (preoperatively), during the intervention period (4-8 weeks before the surgery), in-hospital, and up to 3 months post-operatively, either via face-to-face contact, telephone, text message, e-mail or post, accordingly to the patients’ preferences. During this time, demographic, clinical, and data referent to the trials’ assessment schedules will be collected. Participation in the PRIORITY Trial will not affect surgical waiting time. Recruited participants may choose to withdraw from the study at any stage. All data collected before the time of study withdrawal will be included in data analyses, including clinical information routinely collected during their in-hospital care (e.g., postoperative complications and length of stay).

### Randomisation and blinding

Consenting participants will undergo baseline assessment immediately before randomisation to intervention (prehabilitation with a progressive preoperative exercise and education program) or control group (usual care alone). An experienced biostatistician, not involved in patient recruitment or data collection, will create the randomisation sequence a priori using a central secure (computerised) randomisation service (1:1 allocation ratio in random permuted blocks of sizes 4 or 2 stratified by site, to ensure balance in treatment assignment within the study sites) to ensure concealment of treatment allocation and blinding of the treating surgeon, all trial personnel and the statistician. The randomisation schedule (i.e., allocation tables as Microsoft Excel file) will be uploaded by an independent Research Officer (not involved in the trial) into the PRIORITY TRIAL’s Research Electronic Data Capture (REDCap) database. The REDCap randomisation module will randomise participants into the intervention or control group. Due to the nature of the intervention, it is not possible to blind the clinicians delivering the intervention (exercise and education program); however, we will ensure that all patients’ interactions are standardised.

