
#### Other outcome measures

The following outcome measures will be collected:(i)*Functional capacity*: This will be measured by the CPET at baseline and within 1 week before the scheduled surgery [42]. Improved fitness will be defined as a positive change (≥10% on peak VO_2_, to account for inter-test variability) between CPET tests. Due to coronavirus disease (COVID-19) outbreaks in Australia, some clinics may not be able to see participants face-to-face, and access to CPET will be restricted and will not be uniformly available to all participants.(ii)Duke Activity Status Index (DASI): functional capacity will be measured at baseline and within a week before surgery. The DASI is a 12-item scale in the form of a self-reported questionnaire. The final score ranges from 0 to 58, where a higher score indicates higher functional capacity [43].(iii)*Self-reported physical activity*: Self-reported physical activity will be measured at baseline, within a week before surgery, and postoperatively on discharge day and after 3 months using the following tools: The Active Australia Survey [44], strength questions from the New South Wales Health population survey (https://www.health.nsw.gov.au/surveys/adult/Pages/default.aspx) and sitting questions from the International Physical Activity Questionnaire short form (IPAQ-SF) [45].(iv)*Objective physical activity*: Objective physical activity will be measured during the preoperative period using an activity monitor (Yamax EX510 Activity Tracker). For the intervention group, the activity monitor will be used during the whole intervention period and will provide real-time visual feedback. For the control group, objective physical activity will be collected using an activity monitor without any visual feedback during the 7 days before their second assessment (within 1 week before the scheduled surgery).(v)*Pain intensity*: Pain will be measured on a numerical pain rating scale (NPRS; 0 to 10 - where higher scores indicate worst symptoms) [46] at baseline, within a week before surgery, and postoperatively on discharge day and after 3 months.(vi)*Satisfaction*: Patient satisfaction of the intervention will be measured at the follow-up visit within 1 week before surgery using a self-reported questionnaire [33].(vii)*Fatigue*: Fatigue will be measured using the Fatigue Severity Scale at baseline, within 1 week before surgery and postoperatively on discharge day and after 3 months [47].(viii)*Five Times Sit-to-Stand Test*: Lower limb strength and function will be measured using the five times sit-to-stand test [48]. Patients will sit with arms folded across their chest and back against a chair. Then, patients will be instructed to stand up and sit down five times as quickly as possible, and the time taken to complete the test will be recorded. Due to COVID-19 outbreaks in Australia, participants will have the option to perform this assessment via video call.(ix)*Six-Minute Walk Test (6-MWT)*: Aerobic capacity and endurance will be measured using the 6-MWT. The test will be performed using the American Thoracic Society (ATS) guidelines indoors, along a flat, straight, enclosed corridor at each participating site [49]. The course will be 30 m in length and marked every three meters. The starting line and turning points will be marked and indicated to patients. Patients will be instructed to rest before beginning the test near the starting position, a forehead sensor and pulse oximeter will be attached to the patient for SpO2 and heart rate measurements, a timer will be set to 6 min, and a standardised guide will be used to provide instructions to patients. Patients will be informed that the objective of the test is to walk as far as possible for 6 minutes but are permitted to slow down, stop or rest when required. The distance walked will be recorded. Due to COVID-19 outbreaks in Australia, some clinics may not be able to see participants face-to-face. Thus, the 6-MWT assessment will be restricted and will not be uniformly available to all participants.(x)*Adherence to the study exercise program*: Defined as the percentage of exercise sessions attended/performed by those patients randomised to the preoperative intervention group. This will be collected using the clinician activity record. In addition, participants will receive the participant exercise diary to document their supervised sessions, home exercises, and physical activity advice. Participants will be contacted every week by the trials’ research officer to report their adherence to the preoperative program. Successful adherence to the preoperative program will be defined as ≥70% attendance of the supervised sessions.(xi)*Adverse events*: Defined as any undesirable event, such as injury, fall, severe breathlessness, new or progressive pain, and progressive fatigue will be collected preoperatively during or up to 60 min following the trial intervention or outcome assessment. Serious adverse events will be defined as life-threatening or result in disability, incapacity, hospitalisation, or death during or up to 60 min following the trial intervention or outcome assessment. In serious adverse events, the trial chief investigator and trial research officer will be notified immediately, and the incident reported to the relevant hospital ethics committee.(xii)*Treatment and Health Services*: Use of treatment and health services will be collected (via follow-up questionnaire) up to 3 months after surgery for the cost-effectiveness analysis. This would include information about treatments (physiotherapy, etc.), diagnostic imaging, visiting GP/specialist clinics, emergency department visits, and hospital readmissions.

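### The research officer role that seeks consent also has weekly contact that reveals the intervention arm; with blocks of 2 or 4 within site this makes later allocations partly predictable and contradicts the claim that all trial personnel are blinded

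*Protocol article*

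**What the plan says.** The Trial design section describes "two parallel groups randomised in a 1:1 allocation", and Study sites names three centres. Randomisation and blinding specifies "random permuted blocks of sizes 4 or 2 stratified by site" and gives as its purpose "to ensure concealment of treatment allocation and blinding of the treating surgeon, all trial personnel and the statistician". The only exception made there is that "it is not possible to blind the clinicians delivering the intervention". The Discussion adds that participants are not blinded either.

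Three other places bear on this:

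- **Participant recruitment and mode of contact:** the trial's "research officer will seek consent from patients", and research officers at the institutions take part in identifying and screening patients.
- **Other outcome measures, adherence item:** participants are contacted each week by the trial's "research officer to report their adherence to the preoperative program". Adherence is defined only for patients randomised to the intervention.
- **Interventions, intervention group:** the same role sends weekly diary reminders to treating clinicians and participants, and a research team member checks compliance by message or call.

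**The concern.** Two problems follow. First, the blinding statement cannot be true of a role that discusses exercise adherence with intervention patients every week. Second, that role is also the one that enrols. A central REDCap list hides the next allocation only from someone who does not know the earlier ones. With very small blocks inside each site, the running imbalance carries much of the information about what comes next.

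An enroller who has a good idea of the next arm may, without intending to, time or encourage consent differently for fitter and frailer patients. One exclusion criterion, comorbidity that prevents exercise, calls for judgement. Such selection would enter the primary chi-square comparison directly. Blinded outcome extraction does not address it, and covariate adjustment removes only the part explained by measured covariates.

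**Working it through.** **Does the role learn allocations?** Adherence is an intervention-arm measure, so the content of the weekly contact identifies the arm. Among enrolled patients, the absence of such contact identifies controls. If controls were also contacted weekly, the content would still differ.

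**Does it learn them in time?** Assume equal sites: 172/3 is about 57 patients per site. Trial status gives June 2021 to the end of 2024, with a pause, so roughly 36 to 43 months. That is 57/43 = 1.3 to 57/36 = 1.6 patients per site per month, or about one every three weeks. Weekly contact would usually reveal the last allocation before the next one is made.

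**How predictable is the next arm?** The article gives no predictability figure to reproduce. Inputs from the article are 1:1 allocation and blocks of 2 or 4 within site. Assumptions are that the two sizes are equally likely, and that one observer knows all earlier allocations at the site but not the size of each block. The observer guesses whichever arm is behind, and tosses a coin when the arms are level.

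- Block of 2: expected correct = 1/2 + 1 = 1.5 of 2. The site is unbalanced before 1 allocation, and that guess is always right.
- Block of 4: expected correct = 1/2 + 2/3 + 2/3 + 1 = 2.83 of 4. The site is unbalanced before 1 + 1/3 + 1 = 2.33 allocations, of which 2/3 + 1/3 + 1 = 2 are guessed correctly.
- Equal mix: correct overall = (1.5 + 2.83)/6 = 72.2%. Unbalanced = (1 + 2.33)/6 = 55.6%. Correct when unbalanced = (1 + 2)/(1 + 2.33) = 90.0%.
- Certain allocations: a block of 4 opens with two of the same arm with probability 1/3, and the next two are then known. This gives (1/3 × 2)/6 = 11.1%.

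In numbers, 55.6% of 172 is about 96 allocations made while a site is unbalanced. Correct guesses would be about 124 of 172, against 86 by chance.

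**Comparison with other block sizes** (equal mix within each set; the 2.4% is from simulation):

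| Block sizes | Correct overall | Unbalanced share | Correct when unbalanced | Certain |
|---|---|---|---|---|
| 2 and 4 (plan) | 72.2% | 55.6% | 90.0% | 11% |
| all 2 | 75.0% | 50.0% | 100% | not plan |
| all 4 | 70.8% | 58.3% | 85.7% | not plan |
| 4, 6 and 8 | 68.1% | 63.8% | 78.4% | 2.4% |

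The middle rows bound the effect of the unstated mix on the first and third figures.

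The drop from 90% to 78% must be read with the unbalanced share. Correct guesses made while unbalanced are 0.556 × 0.900 = 0.50 of allocations in the plan and 0.638 × 0.784 = 0.50 with 4, 6 and 8. In any balanced block, half the steps return towards balance. The net gain from larger blocks is therefore about 4 percentage points overall.

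**The case against.** The strongest reply is that the article describes roles, not people. It speaks of research officers in the plural for screening, the trial's research officer for consent and adherence, and a research team member for compliance checks. Who does what at each site may be settled in a delegation log that an article would not reproduce. This stands as a limit: overlap in one person is not shown. But the article gives consent and weekly adherence contact to the same named role and states no separation, so the blinding claim conflicts with its own text as written.

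Several features also limit selection. Participants are to be consecutive, screening numbers and reasons for ineligibility are recorded, several professions identify patients, randomisation follows consent and baseline assessment, and the 4 to 8 weeks before surgery leave little room to delay. Outcome extraction, data management and analysis are stated to be blinded. These reduce the opportunity or protect outcome assessment; none prevents inference from past allocations.

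A reader might infer that the next allocation is as good as known. The figures do not support that: at 44% of allocations the site is level and the guess is a coin toss, and only about 11% are certain. A reader might also infer that larger blocks would solve the problem; on their own they change little.

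**Conclusion.** The point holds in two parts. The statement that all trial personnel are blinded is inconsistent with the duties the article gives to the research officer. The same overlap, combined with published blocks of 2 or 4 within site, would let an informed enroller guess the next arm about 72% of the time (71% to 75% across possible mixes).

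This figure assumes one observer who knows every earlier allocation at the site; partial knowledge would bring it closer to 50%. The 11% assumes an equal mix. The documents do not support the stronger conclusion that concealment has failed or that the complication comparison is biased: what is computed is guessing accuracy, not its effect on the result. It is an avoidable weakness that is cheap to close.

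**What to change.** **Main change.** Assign adherence and diary contact at each site to an existing team member who does not screen, consent or assess patients there. Contact may be by message or call, so it could be handled from another site; because allocation is stratified by site, one site's allocations do not help predict another's. Replace the blinding sentence with a list: blinded are surgeons, outcome extractors, the data manager and the statisticians; not blinded are participants, treating clinicians and the adherence contact. If the duties are already separated in practice, say so. The cost is reassignment of one task and a corrected sentence.

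**Secondary change, of modest effect.** For allocations not yet used, drop blocks of 2 and use larger random sizes, for example 4, 6 and 8, withheld from recruiting staff. Correct guesses fall from 72% to 68% overall and certain allocations from about 11% to 2.4%. The cost is a new allocation table and a maximum imbalance per site that rises from 2 to 4 patients. The benefit depends on how much recruitment remains, which the article does not state.
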